### Study aims

2.1

The main goal of this study is to determine the effect of supplementation with ginger on neurofilament light chain, matrix metalloproteinase‐9, interleukin‐17, nitric oxide, complete and differential blood counts, disability status, quality of life, gastrointestinal symptoms, and BMI in patients with relapsing‐remitting MS. The primary outcomes are interleukin‐17, nitric oxide, and disability status. The secondary outcomes are neurofilament light chain, matrix metalloproteinase‐9, complete and differential blood counts, quality of life, gastrointestinal symptoms, and BMI.

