### Sample size and sampling method

2.5

Given the study design and the existence of two independent groups, the following formula will be used to determine the required sample size:

$$n=\frac{{\left(Z_{1-\frac{\alpha }{2}}+Z_{1-\beta }\right)}^{2}\left(s_{1}^{2}+s_{2}^{2}\right)}{{\left(\mu_{1}-\mu_{2}\right)}^{2}}\;$$

Considering interleukin‐17 as one of the primary outcomes of this study, the number of samples in each of the intervention and control groups was determined to be 13 people (in total 26). The calculations were performed by assuming the type I error equal to 0.05 and the test power equal to 90% and by taking into account *S*
_1_ = 4.07, *S*
_2_ = 9.19, and the effect size equal to 9.28 based on the previous report.^30^

Considering nitric oxide as one of the primary outcomes of this trial, the number of samples in each of the intervention and control groups was determined to be 22 people (in total 44). The calculations were conducted by assuming the type I error equal to 0.05 and the test power equal to 90% and by taking into account *S*
_1_ = 0.72, *S*
_2_ = 0.19, and the effect size equal to 0.5 based on the previous report.^31^

Considering disability status measured by EDSS^9^ as one of the primary outcomes of the present study, the number of samples in each of the intervention and control groups was determined to be 22 people (in total 44). The calculations were done by assuming the type I error equal to 0.05 and the test power equal to 90% and by taking into account *S*
_1_ = 0.29, *S*
_2_ = 1.06, and the effect size equal to 0.74 based on the previous report.^32^

Finally, according to the maximum number of the samples (22 people in each group and 44 in total) and considering a drop‐out rate of ∼20%, the required sample size was estimated to be 26 patients in each group and 52 in total. The participants will be selected using convenience sampling method.

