#### Gastrointestinal symptoms

2.10.5

The frequency and severity of 12 gastrointestinal symptoms including anorexia, dysphagia, heartburn, nausea, vomiting, abdominal pain, bloating, belching, flatulence, constipation, diarrhea, and fecal incontinence will be evaluated using the self‐reported Visual Analog Scale (VAS) ranging from 0 (best) to 100 mm (worst). This method has been previously used by Preziosi et al. to assess gastrointestinal symptoms in MS patients.^41^ The MCID for VAS of gastrointestinal symptoms has been considered 10 mm.^42^

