### Statistical analysis

2.13

SPSS Statistics software version 26 will be used for statistical analysis of data. The Shapiro–Wilk test and skewness will be applied to investigate the normal distribution of quantitative variables. Mean ± standard deviation or median [interquartile range] will be used to report quantitative variables, and number (percentage) will be used to report qualitative variables. For each outcome, the estimated effect size and its 95% confidence interval will be presented. The paired *t*‐test or Wilcoxon signed‐rank test will be performed to compare within‐group differences in quantitative variables. The independent *t*‐test or Mann−Whitney *U* test will be conducted to compare between‐group differences in quantitative variables. The analysis of covariance will be applied to compare between‐group differences by adjusting confounders. The Pearson *χ*
^2^ test or Fisher's exact test will be performed to compare between‐group differences in qualitative variables. All tests will be two‐tailed with a significance level of 0.05. The Statistical Analyses and Methods in the Published Literature (SAMPL) guideline will be followed for reporting statistical results.^46^

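### Three primary outcomes are each tested at 0.05 with no rule for what counts as success: if any one suffices, the family-wise error can reach about 14%; if all three are required, joint power is about 77% under independence, not 90%

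*Protocol article*

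**What the plan says.** Three places in the protocol article bear on this.

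- **Section 2.1, Study aims:** "The primary outcomes are interleukin‐17, nitric oxide, and disability status". The three are listed with no order and no hierarchy.
- **Section 2.5, Sample size and sampling method:** a separate calculation is made for each primary outcome, each assuming "the type I error equal to 0.05 and the test power equal to 90" per cent. The stated results are 13, 22 and 22 per group for interleukin-17, nitric oxide and EDSS. The largest, 22, is carried forward and raised to 26 per group for drop-out.
- **Section 2.13, Statistical analysis:** every test is two-tailed "with a significance level of 0.05".

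The article does not say how many of the three primaries must be significant, and gives no split of alpha and no testing order.

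**The concern.** With three primary outcomes, the reader needs to know what result would make the trial positive. Two rules are common. Under the first, success on any one primary is enough, and the 0.05 must then be shared among the tests or protected by a sequential procedure. Under the second, all three must succeed. Each can then keep 0.05, but the relevant power is that of winning all three together.

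The plan adopts neither. It gives each outcome the full 0.05, which is valid only under the second rule, and plans 90% power outcome by outcome, which describes the trial only under the first. Whichever rule was meant, one of the two stated properties fails. The practical risk is that one significant serum marker out of three primaries is reported as a positive trial. The Background (section 1) states that the authors know of no earlier randomized trial of ginger in MS, so such a claim would carry weight.

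**Working it through.** **Inputs (section 2.5).** Standard deviations and difference: interleukin-17 4.07, 9.19 and 9.28; nitric oxide 0.72, 0.19 and 0.5; EDSS 0.29, 1.06 and 0.74. Two-sided alpha is 0.05, power 90%, and 22 evaluable patients per group.

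**Step 1: the plan's own figures.** The article's formula is n = (z₁₋α/₂ + z₁₋β)² (s₁² + s₂²) / d², with (1.960 + 1.282)² = 10.507.

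- Interleukin-17: 10.507 × 101.021 / 86.118 = 12.3, so 13 (stated 13).
- Nitric oxide: 10.507 × 0.5545 / 0.25 = 23.3, so 24 (stated 22).
- EDSS: 10.507 × 1.2077 / 0.5476 = 23.2, so 24 (stated 22).

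The stated sizes are reproduced to within two patients per group. They follow from an unadjusted two-sided 0.05; a one-sided 0.05 would give 11, 19 and 19. So the sample size makes no allowance for multiplicity.

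**Step 2: power for each outcome at 22 per group, alpha 0.05.** Power = Φ(d / √((s₁² + s₂²)/22) − 1.960).

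- Interleukin-17: Φ(4.331 − 1.960) = 99.1%.
- Nitric oxide: Φ(3.149 − 1.960) = 88.3%.
- EDSS: Φ(3.158 − 1.960) = 88.5%.

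**Step 3: if any one primary suffices.** With all three null hypotheses true and independent tests, the family-wise error is 1 − 0.95³ = 14.26%. The upper bound under any dependence is 3 × 0.05 = 15%. The article gives no correlations, so a range was simulated with three equally correlated two-sided z-tests:

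| Assumed pairwise correlation | Chance of at least one false positive |
|---|---|
| 0 | 14.3% |
| 0.3 | 13.6% |
| 0.5 | 12.5% |
| 0.7 | 10.9% |
| 0.9 | 8.4% |
| 1 | 5.0% |

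**Step 4: if all three are required.** The chance of falsely declaring success stays at or below 5%. Joint power under independence is 0.991 × 0.883 × 0.885 = 77.4%. Positive correlation raises this, but it can never exceed the weakest component, 88.3%.

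**Step 5: power with multiplicity control at 22 per group.** The strictest Holm step uses 0.05/3 = 0.0167, with critical value 2.394.

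- Interleukin-17: Φ(4.331 − 2.394) = 97.4%.
- Nitric oxide: Φ(3.149 − 2.394) = 77.5%.
- EDSS: Φ(3.158 − 2.394) = 77.8%.

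Full Holm, simulated with all three effects at their planned size, gives 98.8% for interleukin-17 and about 87% for nitric oxide and EDSS when outcomes are independent. At a correlation of 0.5 the latter two are about 86%.

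**The case against.** The best counter-argument is that 14% is conditional. It needs independent tests, three true null hypotheses, and a rule that any single significant primary counts. The article states none of these. Interleukin-17 and nitric oxide are both serum measurements (section 2.10.2), and section 1 links both to MS pathology and immunomodulation, so some correlation is plausible. The success rule could also be the strict one, since sizing for the largest n fits requiring all three as well as it fits three separate claims. A success rule may also sit in an analysis plan that is not shown.

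The first part stands: a reader might infer that the trial's error rate simply is 14%, and the documents do not support that. The last part does not remove the concern. The article is not merely silent: section 2.13 fixes 0.05 for all tests and section 2.5 gives the full 0.05 to each primary. An analysis plan that adjusted alpha would contradict the first and undercut the power stated in the second. If the strict rule was meant, the 90% is not the trial's power.

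A reader might also extend the criticism in two directions, and neither is supported.

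- **Gastrointestinal symptoms.** Section 2.10.5 refers to "The frequency and severity of 12 gastrointestinal symptoms", which could be read as 24 separate tests with a near-certain chance finding. The article does not say that each item is tested separately, the symptoms are unlikely to be independent, and these are secondary outcomes, which are commonly tested without adjustment.
- **Within-group tests.** Section 2.13 lists paired tests, but it also plans between-group tests and analysis of covariance. Nothing says that conclusions will rest on within-group change.

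**Conclusion.** The concern holds for the three primary outcomes, in conditional form.

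- If any one significant primary may be claimed as success and all three null hypotheses are true, the family-wise error is up to about 14% (15% at the very most). It is 14.3% under independence, 12.5% at an assumed correlation of 0.5 and 10.9% at 0.7, against the stated 5%.
- If all three must be significant there is no inflation, but joint power at 22 per group is about 77% under independence, against the stated 90%.

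The correlations are assumptions, and the power figures rest on the article's own standard deviations and differences. The conclusion that does not depend on them is that the plan fixes the level of every test without fixing what the trial has to show.

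**What to change.** Choose one of two rules and record it, with its power, before the allocation is unblinded.

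1. **Holm (preferred if any one primary may support a claim).** Order the three primary p-values. Compare the smallest with 0.05/3, the next with 0.05/2 and the last with 0.05, stopping at the first that fails. Suggested wording: *The three primary outcomes will be tested with Holm's procedure at a two-sided family-wise level of 0.05.* Restate power at 22 evaluable per group: about 86 to 87% for nitric oxide and EDSS if all three effects are real, and about 78% at the strictest step, compared with about 88% unadjusted by the article's own formula.
2. **All three required.** State that the trial is positive only if all three are significant at 0.05, and give the joint power of about 77% under independence.

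The cost is a sentence in section 2.13 and a restated power in section 2.5. No patients or data are added and blinding is unaffected. The price of Holm is lower power for each primary outcome, and 78% against a planned 90% is not trivial. Restoring 90% at 0.0167 would take 30 evaluable per group for nitric oxide and EDSS, or 30 / 0.80 = 37.5, so 38 per group with 20% drop-out. Section 2.2 says the trial is already in progress, so stating the lower power openly is the more realistic course.

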## ETHICS STATEMENT

This study is in agreement with the Declaration of Helsinki and its later amendments and has already been approved by the Medical Ethics Committee of Isfahan University of Medical Sciences with the ethics code IR.MUI.RESEARCH.REC.1400.248. Before enrollment, both oral and written informed consent will be obtained from the participants.

## Data Availability

Data sharing is not applicable to this article because no datasets are currently generated or analyzed.
